### Data analysis

*Qualitative data* Qualitative data sources include open-ended survey questions, interviews with clinical staff and focus group data. We will initially use a deductive, directed content analysis approach, as described by Hsieh and Shannon (2015), guided by CFIR, to analyze barriers and facilitators to implementation [39]. To provide a more in-depth description of patient and caregiver experiences with and perceptions of MBC, as well as clinical staff’s experiences (separately) a second analysis of qualitative data will be performed using inductive, conventional content analysis [39]. Qualitative data analysis will be performed using NVIVO qualitative data analysis software [40].

*Staff survey data* Descriptive statistics will be calculated for demographic and closed-response questions from the survey.

*De-identified EHR data* To specifically examine penetration of the intervention in The Summit, the percentage of patients participating in MBC (i.e., filling out PROMs) will be calculated using the total number of patients enrolled in the services compared with the number of patients who responded to PROMs. The percentage of patients filling out PROMs at intake, midpoint and discharge will also be calculated (as a measure of fidelity and penetration).

*PROMs data* The PROMs data of those who consented to research use will be used to perform subgroup analyses by service (i.e., walk-in, day program, intensive community treatment) and by patient demographics (e.g., age, sex, gender, spoken language, education level).

To examine the validity of the chosen PROMs for use in MBC in this population, analyses of item quality, construct validity and responsiveness (ability to capture change) will be performed on the PROMs data of those who consent for their data to be used. Item analysis will be performed by calculating descriptive statistics for the individual items in each PROM will be calculated (median of the responses, the frequency of endorsement, i.e., the proportion of people choosing each response option, and non-response rates i.e., percent of missing data). Construct validity of the PROMs will be evaluated using a hypothesis-testing approach recommended by the COSMIN group [41]. Responsiveness of the measures will be evaluated using Guyatt’s responsiveness ratio [42].

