### Intervention description

Measurement-Based Care (MBC) is a commonly used term to describe the routine clinical use of PROMs in mental health services [22]. It is accepted that MBC consists of three main steps: (1) administering a symptom, outcome, or process measure (i.e., PROM) ideally before a clinical encounter; (2) clinician and patient review of PROM data; (3) collaborative re-evaluation of the treatment plan informed by data [24].

MBC will be a standard part of care at The Summit. Three PROMs will be administered across all services at the Centre, the acute version of the Pediatric Quality of Life Inventory Generic Core Scales (PedsQL), the Revised Children’s Anxiety and Depression Scale (RCADS-25), and Columbia-Suicide Severity Rating Scale (C-SSRS). These measures were chosen based on the International Consortium for Health Outcomes Measurement’s Set of Patient-Centered Outcome Measures for Children and Young People with Anxiety and Depression, including OCD and PTSD, informed by the PROMs available within the provincial electronic health record (EHR), and in collaboration with patients, caregivers, and researchers [25].

The acute version of the PedsQL is a 23-item questionnaire with a 7-day recall period. It has 4 scales (physical, emotional, social, school functioning) and three summary scores (Physical Health Score, Psychosocial Health Score and Total Scale Score) [26]. It has self-report forms for children in 3 different age groups and parent-report forms for 4 different age groups [26]. RCADS-25 is a 25-item questionnaire for children and youth ages 8–18 with 2 subscales (anxiety and depression) and a total scale score which can be converted to norm-based T scores [27]. It has self-report and parent-report forms. The C-SSRS is a 7-item self-report questionnaire for youth ages 10 and older, which classifies individuals as high, moderate or low risk for suicide [28]. The RCADS-25 and C-SSRS have demonstrated good reliability and evidence of their validity in pediatric mental health populations [27, 28]. The reliability and validity of the PedsQL in this population has not been reported, however in the general population it performs well and is widely used within Alberta’s pediatric health system [29].

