Figure 1 illustrates PROM data collection timepoints for each service. For walk-in services, PedsQL will be administered routinely at intake, with the intake process flagging whether RCADS and C-SSRS need to be administered. For the 2-week day hospital program, all three PROMs will be administered at intake and at discharge. For intensive community treatment services, the three PROMs will be administered at intake, midpoint of treatment (after 2 weeks) and at discharge. In each case, the PROMs will be automatically scored and represented graphically (along with prior PROM scores) in a downloadable summary document which also contains patients’ responses to each item. The summary document will be imported into the patients’ EHR by the intake coordinator for the service. During the clinical encounter, the clinician will access patient scores in the EHR and review them with the patient. Together they will discuss patient concerns highlighted by the PROM and re-evaluate the treatment plan. Whenever possible, PROMs will be administered to both patients and caregivers. A clinician-reported measure, the Children’s Global Assessment Scale (CGAS), will be also be collected at each PROM collection timepoint in the day program and intensive community treatment services, as it is part of the standard of care for children and youth mental health services in Alberta [30].

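### Guyatt's responsiveness ratio is fixed for all the measures, but it does not suit the three-class C-SSRS, and for PedsQL and RCADS-25 its meaning depends on a numerator and a stable group that the article does not tie to it

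*Protocol article*

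**What the plan says.** The Data analysis section (PROMs data) sets out three validity analyses: "analyses of item quality, construct validity and responsiveness (ability to capture change) will be performed on the PROMs data of those who consent". For the third it names a single statistic: "Responsiveness of the measures will be evaluated using Guyatt’s responsiveness ratio". The measures are PedsQL, RCADS-25 and C-SSRS.

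The Intervention description gives their scoring. PedsQL has scale and summary scores. RCADS-25 has subscales and "a total scale score which can be converted to norm-based T scores". For the C-SSRS the article says "The C-SSRS is a 7-item self-report questionnaire for youth ages 10 and older", "which classifies individuals as high, moderate or low risk for suicide". No summed or continuous C-SSRS score is described.

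The same section gives the schedule. Walk-in patients are measured at intake only. The two-week day program measures at intake and discharge. For the third service: "For intensive community treatment services, the three PROMs will be administered at intake, midpoint of treatment (after 2 weeks) and at discharge". The clinician-rated CGAS "will be also be collected at each PROM collection timepoint in the day program and intensive community treatment services". The Data collection section adds clinician-reported scores to the matched extract and plans to relate them to the PROMs. It does not use them to define who is stable or improved.

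**The concern.** Guyatt's ratio divides a change by the SD of change scores in stable patients. The change is either an important difference fixed in advance or the mean change observed in improved or treated patients. Its value as evidence about an instrument depends on which numerator is used and who counts as stable.

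Two things do not fit here. First, one ratio is fixed for all the measures, although the C-SSRS result is an ordered class with three levels. Second, all planned change scores for PedsQL and RCADS-25 come from patients in treatment for acute or escalating problems, and the article does not connect the ratio to a stable group, an improved group or an important difference.

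What is at stake is interpretation. With observed mean change on top, a sound instrument looks unresponsive if patients changed little over a short treatment, and a noisy one looks responsive if they changed a lot. This matters most for PedsQL, because the article says its reliability and validity in this population have not been reported.

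**Working it through.** The article gives no figure for responsiveness, so there is nothing to reproduce. All numbers below are illustrative assumptions chosen to show how the statistic behaves.

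**1. Which services supply change scores**

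| Service | PROM timepoints | Planned change score | CGAS at same timepoints |
|---|---|---|---|
| Walk-in | intake | none | not stated |
| Day program | intake, discharge | yes, under treatment | yes |
| Intensive community treatment | intake, 2 weeks, discharge | yes, under treatment | yes |

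**2. Continuous scores (PedsQL, RCADS-25)**

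Assumptions: error SD 4 per occasion; true-change SD 5; mean true change 2, 5 or 10; an external anchor correlated 0.6 with true change; stable means anchor change within ±2.5; important difference 5.

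- SD of change from error alone: 4 × √2 = 5.66.
- SD of change in all patients: √(5² + 5.66²) = √57 = 7.55.
- SD of change in anchor-stable patients, by simulation of 400,000 patients: about 6.9. It lies above 5.66 because an imperfect anchor lets some true change through.

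| Version of the ratio | Mean change 2 | 5 | 10 |
|---|---|---|---|
| Mean change / SD in all patients (simulated) | 0.27 | 0.66 | 1.33 |
| Mean change / SD in anchor-stable | 0.29 | 0.72 | 1.45 |
| Mean change in anchor-improved / SD in anchor-stable | 0.65 | 0.99 | 1.59 |
| Fixed difference of 5 / SD in anchor-stable | 0.72 | 0.72 | 0.72 |

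The closed form for the first row gives 2/7.55 = 0.26, 5/7.55 = 0.66 and 10/7.55 = 1.32, which agrees with the simulation to within 0.01.

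The instrument is the same throughout. In the first two rows the ratio rises about fivefold only because patients improved more, so a stable-group denominator alone does not cure this. In the third row it still more than doubles. Only the fixed numerator holds steady. For anchor correlations of 0.3 to 0.9 that version lies between 0.67 and 0.82.

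**3. Three-level C-SSRS class**

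Suppose a stable patient moves one class up with probability p and one class down with probability p. Then the SD of change is √(2p). Take an assumed mean change of 0.5 class. The ratio is 0.5/√(2p), and the chance that none of 20 stable patients changes class, which leaves the ratio undefined, is (1 − 2p)^20.

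| p | SD | Ratio | Chance undefined, 20 stable patients |
|---|---|---|---|
| 0.02 | 0.20 | 2.50 | 44% |
| 0.05 | 0.32 | 1.58 | 12% |
| 0.10 | 0.45 | 1.12 | 1% |
| 0.20 | 0.63 | 0.79 | under 1% |

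For the same mean shift the ratio spans 0.79 to 2.50, according only to how often stable patients happen to cross a class boundary. It also treats the step from low to moderate as equal to the step from moderate to high.

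**The case against.** The strongest reply is that this is one sentence of a journal article. The article refers to a detailed evaluation plan in Supplementary File 2, which is not at hand and may define the anchor, the stable group and the important difference. That stands, so the missing definitions alone would be weak ground. It does not reach the C-SSRS mismatch, which is visible in the text shown.

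A reader might also infer three stronger conclusions that the documents do not support:

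- **That the design cannot identify stable patients.** It can. CGAS is collected at each PROM timepoint in both services with repeat measures, and being in treatment does not mean that nobody is stable. The gap is that the article does not link CGAS to the ratio.
- **That the result must reflect treatment effect.** This is conditional. The article does not say that the SD of change in all patients will be used, nor that observed mean change will be the numerator. With a fixed important difference over the stable-group SD, the problem does not arise.
- **That keeping or replacing a PROM hangs on this number.** No such rule appears. Responsiveness stands beside item quality and construct validity, and appropriateness is also judged from surveys, interviews and focus groups.

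The intake-only schedule for walk-in patients is not an error either. The article lists walk-in among its subgroups but does not say that responsiveness will be computed there.

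**Conclusion.** The point holds in a limited form. A ratio of change to SD of change is unsuitable for the C-SSRS as the article describes it, and can be undefined. For PedsQL and RCADS-25 the ratio is usable, but it says something about the instrument only if the numerator is a pre-stated important difference and the denominator comes from patients judged stable by an outside criterion. The article ties it to neither.

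The sizes shown (0.29 to 1.45 against a constant 0.72; 0.79 to 2.50 for three classes) rest wholly on assumed SDs, anchor correlation, important difference and shift probabilities. They show direction and mechanism and do not forecast this study's results. The change is worth making because the data for a better analysis are already planned. The effect on the main objectives is limited, since responsiveness is one secondary part of a formative evaluation.

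**What to change.** Restate the responsiveness analysis as follows, or confirm that Supplementary File 2 already does so.

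1. For PedsQL and RCADS-25, in the day program and intensive community treatment, test pre-stated hypotheses on the direction and size of the correlation between PROM change and CGAS change. This extends to change scores the hypothesis-testing approach that the article already adopts for construct validity. Optionally add the AUC for CGAS-improved versus not improved, with the cut-off stated beforehand.
2. If Guyatt's ratio is kept, restrict it to these continuous scores. Use a pre-stated important difference as numerator and, as denominator, the SD of change in patients whose CGAS change lies inside a pre-stated stable band. Report its confidence interval.
3. Analyse the C-SSRS as an ordinal table of class shifts against CGAS change.
4. State that responsiveness is not assessed in the walk-in service.

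The cost is analysis wording and a little extra work. No new data are needed. The downside is that the CGAS-stable subgroup may be small. In the simulation at anchor correlation 0.6 it was 12% to 23% of patients for mean changes of 10 to 2. With 20 stable patients and normal change scores, the 95% limits for the SD are √(19/32.85) = 0.76 to √(19/8.91) = 1.46 times the estimate. A ratio of 0.72 would then carry limits of about 0.72/1.46 = 0.49 to 0.72/0.76 = 0.95. This is a further reason to make the correlation with CGAS change the main analysis.

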## Discussion

Once the initial implementation process and evaluation are complete, we will have assessed the progress towards the full implementation of MBC at The Summit, as well as identified factors that are affecting implementation. The findings will inform the co-design of strategies with key stakeholders (implementation team, clinical staff, patient and caregiver advisory councils) to address identified barriers and enhance facilitators, and potentially adapt components of the MBC intervention as well as the PROMs workflows.

Previous studies have described the implementation of PROMs within pediatric clinical care settings [43–46], or studied the effectiveness of MBC in child and youth mental health populations [22]. Two studies have evaluated aspects of implementation of MBC in child and youth mental health settings in the United States [47, 48]. To our knowledge, this is the first to study the implementation of PROMs in a publicly funded, Canadian child and youth mental health setting. A systematic evaluation of the implementation of MBC can identify barriers and facilitators, and successful strategies for implementing PROMs in clinical care for child and youth mental health setting. This information can be used to improve future implementation efforts in similar settings.

Foley and Vale (2022) described four key questions to ask during the development of an LHS: (1) what is the rationale for the LHS, (2) what sources of complexity exist in the system; (3) which strategic approaches to change need to be considered; (4) what technical building blocks are needed for a functioning LHS? [14]. The integration of PROMs is one of the aspects considered under the fourth question, the technical building blocks (i.e., collecting data from practice) for developing The Summit as part of an LHS. Other technical building blocks are generating generalizable knowledge from practice data (i.e., analyzing and interpreting data), applying knowledge to practice (e.g., making changes to services, adjusting treatments offered), and learning communities [14]. Learning communities are comprised of multiple stakeholders who come together to address common problems of interest within the LHS [49]. They are at the centre of an LHS, driving the learning and improvement cycles that are key to an effective LHS [14]. In parallel to the implementation of PROMs at The Summit, learning communities will need to be planned and initiatiated [49]. This will involve identifying individuals, developing community structure and governance, sources of funding, defining the problem(s) of interest for the community (e.g., clinical research questions, quality improvement problems), and assessing the data needs for the project [49]. The Summit, with its academic partnership, has many of these elements in place, however processes will need to be formalized, for example, data-sharing agreements and processes between the academic and health system partners need to be established. A structure for a learning community for problem(s) of interest internal to The Summit (e.g., quality improvement initiatives) will also need to be planned.

### Potential issues for this study

We foresee two aspects of this project to create challenges for this evaluation: (1) issues related to change at a newly opening facility, and (2) the research versus quality improvement paradigm that currently exists in health research taking place within health systems.

The Summit is a facility which has yet to begin offering services. Its clinical services were designed based on perceived needs of youth with mental health concerns in Calgary and its staff is completely new. As such, it is likely that The Summit’s operational processes, the services offered and the populations it serves will evolve rapidly in the early stages of opening in response to the needs of patients, to improve workflow efficiencies and as available resources change. This will have two potential effects on this project. The first is that our pre-implementation assessment is limited to a theoretical assessment of barriers and facilitators based on literature, as well as the working group and their professional networks’ experiences of implementing similar interventions in other settings. This evolving assessment could have had substantial impacts on the design of our implementation strategies. Second, the implementation evaluation analyses will have to take into account the changes to The Summit’s operations that are likely to happen in the first year of its operations. Both of these factors increase the complexity of the evaluation and will make it more challenging to accurately describe barriers and implementation outcomes. However, the rate of change at a new facility underscores the need for this formative evaluation, which will uncover and address unanticipated barriers to PROM implemenation.

The second challenge relates to the distinction between quality improvement projects and research. AHS considers academic research a distinct activity, with different requirements than quality improvement projects. The collaboration between the AHS operations team and the academic researchers is foundational to The Summit as an LHS; however, since this evaluation is led by the academic partners, access to data for the evaluation is controlled by research policies within AHS. This has the potential effect of reducing the amount and quality of data that can be used for the evaluation, particularly in terms of the MBC PROMs database, because patients will have to provide informed consent for the use of their PROMs data for this evaluation, and not all patients will consent to this. This will be a limitation to the rigor of this evaluation. Conversely, if this project were run by the health system team, it would be considered a quality improvement project, and while patients should still be consenting to have their data used in quality improvement projects, the data informing this evaluation might be more comprehensive. This problem will also affect other learning activities within The Summit, and has been identified as an issue that hinders learning within health care systems more broadly [11, 50].

## Conclusion

Establishing the components of an LHS is one path towards providing high-value services to meet the growing demand for child and adolescent mental health care. PROMs data, generated as part of clinical care, feed into the LHS and also are suggested as a specific intervention, MBC, to improve outcomes for patients with mental health concerns. However, the implementation of PROMs is challenging, and the literature to guide the process is child and youth mental health is limited. This study has the potential to make a meaningful contribution to the science of implementing PROMs in services for this population.

## Data Availability

Not applicable.

## Abbreviations

AHS: Alberta health services
LHS: Learning health system
VBHC: Value-based health care
PROM: Patient-reported outcome measure
PedsQL: Pediatric Quality of Life Inventory Generic Core Scales
RCADS-25: Revised Children’s Anxiety and Depression Scale
C-SSRS: Columbia-Suicide Severity Rating Scale
EHR: Electronic health record
CGAS: Children’s Global Assessment Scale
QIF: Quality implementation framework
MBC: Measurement-based care
IRLM: Implementation research logic model
CFIR: Consolidated framework for implementation research
